### Research aims

The objective of this research is to determine the incidence of response to VO_2_max after implementation of a standardized (%HRR) and individualized (based on first ventilatory threshold [VT1] and second ventilatory threshold [VT2]) approach to exercise prescription in a community wellness program for 12 weeks. The primary measurement outcome will be VO_2_max with secondary outcomes of total cholesterol (TC), high-density lipoprotein (HDL), low-density lipoprotein (LDL), triglycerides, blood glucose, and resting heart rate (HR) and blood pressure (BP). Thus, the main research aim is to determine whether an individualized exercise prescription decreases the incidence of non-response to CRF and cardiometabolic measurements compared to the standardized approach. Similarly, another primary research aim is to determine if changing the prescription of CRF intensity for a subsequent 12-week intervention elicits more responsiveness in previously categorized non-responders (based on VO_2_max responses). A key secondary aim of this research is to establish whether there are differences in the time course changes of VO_2_max and cardiometabolic risk factors between the experimental groups every fourth week during the 12-week intervention.

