#### Biological variability

Intraclass correlation (ICC) of variation, typical error and co-efficient of variation (CV) for VO_2_max, resting HR, resting BP, and fasting blood glucose, total cholesterol, HDL, and LDL will be calculated as described previously [26]. The CV will be combined with the measurement error of the testing to determine the TE. The TE will be used to categorize responders and non-responders. In summary, for all criteria tested the changes in pre- to post- intervention will be analyzed with responders having a change > TE and non-responders having a change that is ≤ TE.

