#### Incidence of response

Delta values (Δ) will be calculated (post-testing minus baseline value divided by baseline value) for percent change in relative VO_2_max, TC, HDL, LDL, resting BP and resting HR and participants will be categorized as: ‘1’ = responder (% Δ > TE) or ‘0’ = non-responder (% Δ ≤ TE). Chi-squared (*χ*
^2^) tests will be subsequently used to analyze the point prevalence of responders and non-responders to exercise training separated by exercise intensity group (individualized and standardized) between baseline and the end of the end the first 12-week intervention. Only participants who complete ≥ 70% exercise training sessions and strictly adhere to target exercise intensity will be included in the statistical analysis. The probability of making a type I error will be set at *p* ≤ 0.05 for all statistical analyses.

In order to make inferences about the true values (population values) of the effect of both exercise interventions on VO_2_max and cardiometabolic factors, the uncertainty in effect will be expressed as 90% confidence limits and the likelihood the true value of the effect represents a substantial and clinically meaningful change (harm or benefit). Effects will be declared unclear if the confidence interval overlapped thresholds for substantiveness or the effect could be substantially positive and negative or beneficial and detrimental. All probabilistic magnitude-based inferences will be calculated using a published spreadsheet [27].

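### The responder rule uses one signed percent change for all six variables, so every fall in total cholesterol, LDL, resting blood pressure or resting heart rate is coded as non-response

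*Protocol article*

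**What the plan says.** Under Incidence of response, Δ is computed as "post-testing minus baseline value divided by baseline value" and applied to "percent change in relative VO_2_max, TC, HDL, LDL, resting BP and resting HR". Code 1 or 0 is then assigned by a single rule for all of them: "responder (% Δ > TE) or ‘0’ = non-responder (% Δ ≤ TE". Chi-squared tests compare the resulting codes between the individualized and standardized arms.

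Biological variability gives the same rule for every criterion: "for all criteria tested the changes in pre- to post- intervention will be analyzed with responders having a change > TE". It also says where the threshold comes from: "The CV will be combined with the measurement error of the testing to determine the TE".

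The Methods/Design opening describes non-responders as participants who lack a favorable outcome after 12 weeks. Research aims places non-response in both fitness and cardiometabolic measures within the main aim. It names as secondary outcomes TC, HDL and "low-density lipoprotein (LDL), triglycerides, blood glucose, and resting heart rate (HR) and blood pressure (BP". Categorizing responders and non-responders says each testing measurement will be classified, with VO2max as the overriding label.

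**The concern.** A signed change with a positive cut-off works only where a higher value is better. That is so for VO2max and HDL. For TC, LDL, resting BP and resting HR, benefit is a negative Δ, and the rule has no absolute value, sign reversal or direction clause to deal with this. Someone whose LDL falls well beyond measurement noise is coded a non-responder; someone whose LDL rises by the same amount is coded a responder.

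At stake is the cardiometabolic half of the main aim. These are secondary outcomes, but the protocol's question is whether individualized prescription reduces non-response in them, and the 0/1 codes are the direct input to that comparison.

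**Working it through.** The plan gives no numerical TE and no expected change in these variables, so there is no stated figure to reproduce. The check applies the rule as written and compares it with a direction-adjusted rule.

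**Inputs from the article**
- %Δ = 100 × (post − baseline) / baseline (Incidence of response).
- Code 1 if %Δ > TE, otherwise 0, for all six variables (same section).
- TE combines a coefficient of variation with measurement error, so TE > 0 (Biological variability).

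**Step 1: logic, with no assumed numbers.** Any fall gives %Δ < 0 < TE, hence code 0, whatever its size. A rise up to and including TE is also coded 0. Only a rise above TE is coded 1. For a variable where lower is better, code 1 therefore contains only participants who worsened.

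**Step 2: worked codes.** TE is assumed to be 3%, 5% or 8%; each gives the same codes.

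| Variable | Change | As written | Direction-adjusted |
|---|---|---|---|
| VO2max, HDL | +10% | 1 | 1 |
| VO2max, HDL | −10% | 0 | 0 |
| TC, LDL, systolic BP, resting HR | +10% | 1 | 0 |
| TC, LDL, systolic BP, resting HR | −10% | 0 | 1 |

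**Step 3: size under assumed values.** Let %Δ in a lower-is-better variable be normal with mean m and SD s.
- Share coded responder as written: 1 − Φ((TE − m)/s).
- Share improving beyond TE: Φ((−TE − m)/s).

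With m = −5, s = 8, TE = 5:
- as written: 1 − Φ(10/8) = 1 − Φ(1.25) = 10.6%;
- improving beyond TE: Φ(0/8) = 50.0%.

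With s = 8, m from −3 to −8 and TE from 3 to 8, the written rule gives 2.3% to 22.7% and the direction-adjusted rule 26.6% to 73.4%.

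**Step 4: effect on the comparison of arms.** Take two arms with TE = 5, the same SD of 8, and means of −3 and −8.
- As written: 1 − Φ(8/8) = 15.9% and 1 − Φ(13/8) = 5.2%. The arm with the larger fall appears to respond less.
- Direction-adjusted: Φ(−2/8) = 40.1% and Φ(3/8) = 64.6%.

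This reversal is not general. Take TE = 6, one arm with mean −5 and SD 10, the other with mean −8 and SD 15.
- As written: 1 − Φ(11/10) = 13.6% and 1 − Φ(14/15) = 17.5%. The arm with the larger fall has the higher coded rate, although those coded responder are still the ones who worsened.

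**Step 5: the variable lists side by side**

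| Place in the article | Triglycerides | Glucose |
|---|---|---|
| Research aims (secondary outcomes) | named | named |
| Biological variability (TE list) | not named | named |
| Time course changes (ANOVA list) | not named | not named |
| Incidence of response (Δ list) | not named | not named |

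**The case against.** The strongest reply is that the intent is plain. Methods/Design ties non-response to the lack of a favorable outcome. The paragraph that follows the coding rule separates harm from benefit for the magnitude-based inference. The Discussion, describing two earlier training studies, speaks of improvement beyond TE. On this view the rule is shorthand written with VO2max in mind. That is probably right about intent, but none of these statements amends the coding rule, and the Discussion sentence concerns other studies.

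A related reply is that the wording under Biological variability, "responders having a change > TE and non-responders having a change that is ≤ TE", could mean size of change regardless of sign. That does not rescue the rule: a rise in LDL beyond TE would still count as response, and so would a fall in VO2max. Incidence of response in any case defines Δ with a sign.

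Three stronger readings may tempt a reader, and the article does not support them.
- **That the primary result or the crossover is compromised.** VO2max is coded in the right direction. It is the primary outcome and alone determines entry to the second 12 weeks. HDL is also coded correctly.
- **That the ranking of the arms on cardiometabolic response must reverse.** This follows when the spread is similar in both arms, but not in general, as Step 4 shows. The repeated-measures ANOVA under Time course changes analyses the same four variables as continuous measures and keeps direction, so a miscoding could be noticed there.
- **That triglycerides and glucose have no analysis at all.** The article commits in general terms to classifying each measurement, applies the TE rule to all criteria, and refers to cardiometabolic factors in the magnitude-based inference. What stands is that the named lists do not agree.

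**Conclusion.** The point holds for TC, LDL, resting BP and resting HR, four of the six variables in the responder analysis. Followed as written, the rule codes every improvement in them as non-response, and the chi-squared comparisons that use those codes would not measure what the main aim asks. This is an explicit rule that gives a wrong result, not detail left to a fuller document.

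The direction of the error depends only on the signed Δ and a positive TE, both taken from the article. The percentages rest on assumed means, SDs and TEs under a normal model; they illustrate the mechanism and do not predict this trial's data. The damage is confined to the secondary cardiometabolic responder comparisons. The triglycerides and glucose discrepancy is a minor matter of consistency.

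**What to change.** In both Biological variability and Incidence of response, define response as a change beyond TE in the beneficial direction:
- VO2max and HDL: responder if Δ > +TE;
- TC, LDL, resting BP and resting HR: responder if Δ < −TE;
- otherwise non-responder.

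As a minor addition, align the named lists with Research aims and with the commitment to classify each measurement. Add triglycerides to the TE list, and add triglycerides and glucose to the ANOVA and Δ lists, or state that they will not be classified. If they are classified, use Δ < −TE.

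The cost is a sentence or two of wording and two variable names. Both variables are already measured at baseline and weeks 4, 8 and 12 of the first intervention, so no new data are needed for that comparison. The change should be made before anyone is classified, so that the direction is not chosen with the results in view.

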### Sample size calculation

Sample size was projected with change in VO_2_max as the main outcome variable. The means and standard deviations of a previous study [5] were examined and the effect size for this research study was calculated. Assuming a power of 0.80 was needed and the calculated effect size for change in VO_2_max was 0.30, it was determined that approximately 16 participants would be needed for each group [12]. It is assumed there would be an approximate 20% dropout rate, so the aim will be to achieve 20 participants per group.

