#### Exercise intervention

After the completion of the baseline testing, participants will be randomly allocated to either the individualized or standardized arms at a 1:1 ratio using a computerized stratified minimization sequence. One of the primary investigators will have knowledge of the treatment groups to which participants have been allocated in order to interpret test results and prescribe target exercise intensities. However, this same investigator will not be involved in the implementation of the exercise training programs (to be completed by research assistants) in order to mitigate researcher bias. Participants will then be asked to come to the laboratory on Monday, Wednesday, and Friday to take part in the community wellness program and subsequent research. Upon arrival each day, participants will be asked to rest comfortably for 5 minutes in the seated position. Then, their resting BP and HR will be recorded. Following the resting measurements, participants will complete a 5-minute warm-up starting at a low and progressively increasing intensity until they are ready to begin their CRF exercise session. At this point, participants will be asked to stay within the designated HR (described in further detail below) outlined on their exercise log as determined based on their experimental group and week of experimental trial. At approximately 1/3 and 2/3 the total session time, an exercise physiologist or research assistant will record their current HR, rating of perceived exertion (scale 1–10), intensity of aerobic equipment, and any other pertinent notes. At the end of the CRF exercise session, the participant will be asked to complete a cooldown in which the exercise intensity is gradually reduced. While resistance training is not part of this proposed experiment, it is an integral part of the community wellness program and could be a confounding factor to the overall incidence of response. Therefore, all participants will be asked to complete the resistance training after the CRF training session is completed in order to have consistency among all participants. During the first 4 weeks, there will be no resistance training. During the next 4 weeks (week 4–8), there will be a learning and anatomical adaptation phase to resistance training in which proper technique and range of motion will be emphasized and participants will be acclimated to the resistance training machines. During the last 4 weeks (week 8–12) participants will complete one set of 8–12 repetitions on eight machine-based resistance training exercises and progress to two sets by the end of the 12th week [19].

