
#### Determination of workload

For the standardized group, the workload will be determined based on %HRR and completed based on the following calculation:$$ \mathrm{H}\mathrm{R}\mathrm{R}=\left[\left(\mathrm{Maximal}\kern0.5em \mathrm{H}\mathrm{R}\hbox{-} \mathrm{Resting}\kern0.5em \mathrm{H}\mathrm{R}\right)\times \mathrm{Desired}\kern0.5em \mathrm{Percentage}\right]+\mathrm{Resting}\kern0.5em \mathrm{H}\mathrm{R} $$

For the individualized group, the workload will be determined based on ventilatory threshold values as previously described [5, 20] to determine VT1 and VT2. The criteria used for determining VT1 and VT2 will be a visual analysis of figures of time plotted against the relative respiratory variable – ventilatory equivalents of oxygen (VE/VO_2_) and ventilatory equivalents of carbon dioxide (VE/VCO_2_). Determination of VT1 will be an increase in VE/VO_2_ with no increase in VE/VCO_2_ and moving away from linearity of VE, whereas VT2 will be a simultaneous increase in both VE/VO_2_ and VE/VCO_2_. Calculations of HR values associated with ventilatory threshold (VT) values will be calculated prior to exercise sessions and with following HR ranges:Target HR > VT1 = HR range of 10 bpm below VT1 to the HR at VT1Target HR ≥ VT1 to < VT2 = HR range of 15 bpm above VT1 and below VT2Target HR ≥ VT2 = HR range of 10 bpm above VT2

Exercise volume will be prescribed based on energy expenditure per kg of body weight a week (kcal · kg^−1^ · week^−1^) to implement an isocaloric exercise volume (i.e., in terms of kilocalories [kcal] per kg a week) across individuals and groups. Previous research has found that energy expenditure ranging from 4 kcal · kg^−1^ · week^−1^ [21] to 23 kcal · kg^−1^ · week^−1^ [22–25] have positive effects on CRF and cardiometabolic responses to exercise. Therefore, this study will utilize a similar 12-week exercise protocol as previously described [5], while implementing a standardized isocaloric volume (kcal · kg^−1^ · week^−1^) instead of a designated time for each exercise session. Exercise progression will follow standard guidelines that have been previously established [4]. Figure 2 illustrates the exercise progression following baseline testing through the 12-week intervention for both experimental groups while Tables 1 and 2 show the SPIRIT study schedule for experimental and control participants, respectively.

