#### Time course changes

Measures of centrality and spread will be presented as mean ± standard deviation (SD) and ranges will be reported for each measure. The precision of estimates will be reported as 90% confidence limits. Baseline-dependent variables will be compared using general linear model (GLM) ANOVA and Tukey post hoc tests, when applicable. Because baseline and every fourth week program data will be available after the completion of the first 12 weeks the effect of training on CRF (VO_2_max) and cardiometabolic measurements (TC, HDL, LDL, resting BP, and resting HR) will be determined using repeated-measures GLM-ANOVA with the exercise intensity (individualized or standardized) as the between subjects factor. Between group 12-week changes will be analyzed using GLM-ANOVA and Tukey post hoc tests, when appropriate. The assumption of normality will be tested by examining normal plots of the residuals in ANOVA models and will be regarded as normally distributed if Shapiro-Wilk tests are not significant [12]. Effect sizes will be calculated using means and pooled standard deviations. Method of data analysis will be analysis by treatment administered. Only participants who complete ≥ 70% exercise training sessions and strictly adhere to target exercise intensity will be included in the statistical analysis. The probability of making a type I error will be set at *p* ≤ 0.05 for all statistical analyses.

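### The randomised comparison is planned only in participants who attended and kept to an arm-specific intensity target, with no analysis of all randomised participants named

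*Protocol article*

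**What the plan says.** Participants are randomised between two training prescriptions: "participants will be randomly allocated to either the individualized or standardized arms at a 1:1 ratio using a computerized stratified minimization sequence" (Exercise intervention). The comparison of those arms is the core of the trial: "the main research aim is to determine whether an individualized exercise prescription decreases the incidence of non-response to CRF and cardiometabolic measurements" (Research aims).

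The analysis set is fixed in the Statistical analysis section. Under Incidence of response: "Only participants who complete ≥ 70% exercise training sessions and strictly adhere to target exercise intensity will be included in the statistical analysis". The same sentence stands under Time course changes, which also covers the between-group comparison of 12-week changes, and which adds: "Method of data analysis will be analysis by treatment administered". No analysis of all randomised participants is named anywhere in the article.

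The intensity target depends on the arm (Determination of workload): "For the standardized group, the workload will be determined based on %HRR" and "For the individualized group, the workload will be determined based on ventilatory threshold values". Intensity during a session is documented by spot readings: "At approximately 1/3 and 2/3 the total session time, an exercise physiologist or research assistant will record their current HR" (Exercise intervention). The article does not say how far, or how often, a reading may leave the target before a participant stops counting as adherent.

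On losses, Sample size calculation says: "It is assumed there would be an approximate 20% dropout rate". This takes 16 per group to 20.

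**The concern.** Randomisation makes the arms comparable at baseline. It does not make the subsets who later attend and stay on target comparable. Attendance of at least 70% is the same test in both arms, but keeping to target intensity is not, because the target itself is what the trial varies. How well people can hold a prescribed zone is part of what distinguishes the two prescriptions.

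People who cannot hold their zone may also gain less VO2max. If so, removing them raises the responder share of the arm they leave, and an arm that loses more of them gains more from the removal. Non-response is the quantity being compared, so the rule acts directly on the main result. The adherent set is the only set named for that comparison, not one of several.

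Two features add to the problem. First, without a stated tolerance, who is excluded is open to judgement. Second, every exclusion beyond dropout reduces a small sample.

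**Working it through.** **Plan's own figure.** 16 / (1 − 0.20) = 20 per group, which reproduces. The move from 16 to 20 is fully used by the 20% loss.

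**Bias when the arms truly do not differ.** Inputs, all assumed because the article gives no adherence or response rates:
- true response 75% in both arms;
- 25% excluded in one arm and 10% in the other;
- correlation r between ability to adhere and VO2max gain of 0.1, 0.3 or 0.5, with both normally distributed.

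Excluding the least adherent fraction q shifts the mean gain of those who remain by r·φ(z_q)/(1 − q), in SD of change.
- q = 0.25: φ(−0.674)/0.75 = 0.3178/0.75 = 0.424
- q = 0.10: φ(−1.282)/0.90 = 0.1755/0.90 = 0.195
- bias in the mean difference = r × (0.424 − 0.195) = r × 0.229

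The responder share among those who remain is P(gain above the response cut-off and adherence above z_q) / (1 − q), from the bivariate normal distribution.

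| r | responders, 25% excluded | responders, 10% excluded | spurious gap (points) | bias in mean (SD) |
|---|---|---|---|---|
| 0.1 | 76.38% | 75.65% | 0.7 | 0.02 |
| 0.3 | 79.35% | 77.10% | 2.3 | 0.07 |
| 0.5 | 82.70% | 78.77% | 3.9 | 0.11 |

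With equal exclusion in the two arms, both differences are zero. If the arm losing more is the standardized one, the sign reverses.

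**Sensitivity to harsher assumptions.** With 60% true response and 10% versus 40% excluded, simulation gives 62.3% versus 67.7% at r = 0.3 and 64.0% versus 73.3% at r = 0.5. The gaps are about 5 and 9 points.

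**Extreme small-sample case.** If 4 of 20 are excluded in one arm and all 4 are non-responders, 15/20 (75%) becomes 15/16 (94%). Against an untouched 15/20, the pooled proportion is 30/36 = 0.833, so z = 0.1875 / √(0.833 × 0.167 × (1/16 + 1/20)) = 1.50, p ≈ 0.13 without continuity correction.

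**Effect on the analysed number (conditional).** If the 20% covers only people who leave, and a further 15% of the remainder (assumed) fail the adherence rule, 20 × 0.80 × 0.85 = 13.6 per arm. Take a standardised difference of 1.02, roughly what 16 per arm detects with 80% power (two-sided t test). Power is then 88% with 20 per arm, 80% with 16 and 74% with 14.

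**The case against.** The strongest reply is that unequal exclusion is assumed, not documented. The attendance rule is common to both arms. Both intensity targets are heart-rate ranges written on an exercise log and checked by staff in laboratory sessions, and testing every fourth week informs the prescription. Nothing in the article supports 25% versus 10%. This stands: the finding is a risk of bias, and its direction is open.

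A reader might infer that the rule would manufacture a significant benefit for the individualized arm. The figures do not support that. In the 3.9-point scenario, with 15 and 18 analysed, exact enumeration of the uncorrected chi-squared test rejects about 4.9% of the time, against about 4.5% with no selection. The extreme case reaches only p ≈ 0.13. What is at risk is mainly the estimate.

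A reader might also infer that randomisation is thrown away altogether, or that every analysis is restricted. Neither holds. No switching is planned in the first 12 weeks, so treatment administered would normally coincide with allocation; the problem is selection within the arms. The technical-error estimate comes from repeat baseline tests and carries no such rule.

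The article does not define dropout, so it may be meant to include these exclusions. The shortfall below 16 is therefore conditional.

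Finally, an adherent set is a coherent choice for asking what the prescription does physiologically when followed. That justifies it as a secondary analysis, not as the only set for the randomised comparison. Nor is this a detail left to an unseen plan: a plan that analysed everyone would contradict the stated wording.

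**Conclusion.** The concern holds as a stated rule that puts the main comparison at risk of bias. The between-arm analyses of mean change and of incidence of response use only a subset selected after randomisation, on an intensity criterion that is arm-specific and has no stated tolerance, and no all-randomised analysis stands beside them.

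Under the main assumptions the spurious gap runs from 0.7 to 3.9 percentage points (0.02 to 0.11 SD of change), and reaches about 9 points under the harshest set tried. It needs both unequal exclusion and a link between adherence and gain; if either is absent, it is zero. The documents do not establish which arm would benefit. A loss of analysed participants below 16 per arm follows only if dropout excludes non-adherence.

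The mismatch in Determination of workload, where one individualized zone is labelled as above VT1 but given a range that ends at VT1 and starts 10 bpm below it, is a separate inconsistency. A reader might infer that it makes adherence unjudgeable. The article does not show that this label, and not the range on the exercise log, would be used to judge a session.

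**What to change.** 1. Make the primary between-arm analysis all randomised participants in the arm assigned, regardless of attendance or zone adherence, using every available VO2max test (for example a mixed model for repeated measures). Replace the wording on treatment administered accordingly.
2. Keep non-adherers in the week-12 test. It is already scheduled for the experimental groups, so no new visit is needed.
3. Report incidence of response in all randomised participants, with a sensitivity analysis for missing outcomes. Counting missing as non-response is one option, but it penalises the arm with more loss and should not stand alone.
4. Define strict adherence numerically before any outcome is analysed, for each arm's target. Keep the adherent set as a labelled per-protocol sensitivity analysis, and report the number excluded by arm and by reason.
5. State whether the 20% allowance includes non-adherence.
6. Separately, reconcile the VT1 zone label with its range.

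The cost is re-wording the analysis section and the effort of retaining poor adherers for a test already planned. The estimated effect will be somewhat diluted compared with the adherent set; the per-protocol analysis still shows the effect when the prescription is followed.

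### Two competing rules, tests at p ≤ 0.05 and magnitude-based inference on 90% limits, judge the same outcomes with no hierarchy, so the claimed 5% type I error does not cover every declared effect

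*Protocol article*

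**What the plan says.** All of this is in the Statistical analysis section of the protocol article.

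- **Error level.** Both Time course changes and Incidence of response carry the sentence "The probability of making a type I error will be set at *p* ≤ 0.05 for all statistical analyses".
- **First rule.** Time course changes assesses training effects on VO2max, lipids, resting blood pressure and resting heart rate by repeated-measures GLM-ANOVA. It adds: "Between group 12-week changes will be analyzed using GLM-ANOVA and Tukey post hoc tests, when appropriate".
- **Interval level.** The same subsection says "The precision of estimates will be reported as 90% confidence limits".
- **Second rule.** The last paragraph of Incidence of response sets out to draw inferences about population effects on VO2max and cardiometabolic factors. There, "the uncertainty in effect will be expressed as 90% confidence limits and the likelihood the true value of the effect represents a substantial" benefit or harm. The verdict follows from this sentence: "Effects will be declared unclear if the confidence interval overlapped thresholds for substantiveness or the effect could be substantially positive and negative". The tool is named last: "All probabilistic magnitude-based inferences will be calculated using a published spreadsheet".

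The text does not rank the two rules or call either one descriptive.

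**The concern.** A 5% level claimed for every analysis is a statement about every rule by which an effect may be declared. A rule built on 90% limits and likelihoods of benefit does not have that level by construction. Its error rate depends on the threshold for a substantial effect and on how the sentence defining *unclear* is read.

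That sentence joins two conditions that behave very differently: the interval overlaps thresholds, or the effect could be substantial in both directions. If any overlap is enough, the second condition adds nothing. If the second condition is what counts, the rule is far more permissive.

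VO2max is the primary measurement outcome (Research aims), so the conflict reaches the main physiological result. One VO2max difference could be non-significant under ANOVA and clear under the second rule, or significant and yet unclear. The plan does not say which statement would be the trial's conclusion.

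**Working it through.** **Inputs.** From the documents: "approximately 16 participants would be needed for each group" (Sample size calculation); 1:1 allocation; test level 0.05, taken as two-sided; interval level 90%. The plan's inflation for dropout reproduces: 16/(1 − 0.20) = 20 per group. How the 16 was derived does not matter here.

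Assumed: a two-arm difference in SD units with SD 1, and a substantial-effect threshold δ of 0.1, 0.2 or 0.3 SD. The article gives no value; one may be fixed in material not shown, so a range is used.

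**Step 1: cut-points with 16 per arm (30 degrees of freedom).**

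- Standard error: √(2/16) = 0.354 SD.
- Significant at 0.05 if the difference exceeds 2.042 × 0.354 = 0.722 SD.
- Half-width of the 90% interval: 1.697 × 0.354 = 0.600 SD.
- Reading A (*unclear* only if the interval spans both −δ and +δ): clear if the difference exceeds 0.600 − δ, which is 0.40 SD at δ = 0.2.
- Reading B (*unclear* if the interval overlaps any threshold): substantial if the difference exceeds 0.600 + δ, which is 0.80 SD at δ = 0.2.

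At δ = 0.2 the test's cut-point of 0.722 lies between the two, so the rules can disagree under either reading.

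**Step 2: one worked case per reading (δ = 0.2 SD).**

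- Difference 0.65 SD: t = 0.65/0.354 = 1.84, p = 0.076; 90% limits 0.65 ± 0.600 = 0.05 to 1.25; likelihood of benefit 89%. Not significant, but clear under A.
- Difference 0.78 SD: t = 0.78/0.354 = 2.21, p = 0.035; 90% limits 0.18 to 1.38. Significant, but the interval overlaps 0.2, so unclear under B.

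**Step 3: error rates with no true difference.** Simulation of 1,000,000 two-arm trials. The t test at p ≤ 0.05 rejects in 5.0%.

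| δ (SD, assumed) | A: declared clear | B: declared substantial |
|---|---|---|
| 0.1 | 17% | 5.5% |
| 0.2 | 27% | 2.8% |
| 0.3 | 41% | 1.3% |

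With 20 per arm, A gives 18%, 30% and 47%, and B gives 5.0%, 2.4% and 1.0%.

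At these thresholds every significant result is also clear under A. The share of null trials that are clear but not significant at δ = 0.2 is therefore 27.3% − 5.0% = 22.3%.

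Under B at δ = 0.2, 2.2% of null trials are significant yet unclear. An effect declared by either rule occurs in 5.0%, so there is no inflation.

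**Step 4: sensitivity to a likelihood cut-off.** If A also required a likelihood above 75% (assumed), the rates would be 17%, 21% and 13% at δ = 0.1, 0.2 and 0.3, and 4% at 0.5 SD.

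**The case against.** The strongest reply is that the two conditions for *unclear* are joined by *or*, so taken literally any overlap suffices. That is reading B, whose error rate at 0.2 SD is 2.8%. A non-significant result could then be called substantial only if δ were below about 0.722 − 0.600 = 0.12 SD. This stands. A reader might infer that the plan yields positive claims at several times 5%; the documents do not support that as a general statement, because it holds only under reading A. But B makes the second condition redundant, so the text does not settle the reading, and B still allows a significant difference to be called unclear.

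Other points, and what remains of them:

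- **The 90% limits under Time course changes.** They describe precision. Nothing there declares an effect because a 90% interval excludes zero, so they do not themselves break the 5% level. This stands.
- **Clear is not the same as beneficial.** The figures for A count both directions and use no likelihood cut-off. This stands in part; Step 4 shows lower rates, still above 5% for thresholds of 0.1 to 0.3 SD.
- **Thresholds may be set elsewhere.** True, and their absence from an article is not the fault raised. Supplying them would fix the error rate of the second rule but would not say which rule decides.
- **The second rule may concern each programme's own effect.** The wording allows this. The simulated rates apply only to the between-arm contrast, but the repeated-measures ANOVA also tests training effects at 0.05, so two rules would still compete.
- **The main aim is response incidence.** It is tested by chi-squared at 0.05, and this point does not touch it.

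**Conclusion.** The point holds as a conflict between rules. VO2max and cardiometabolic effects are judged both by tests at p ≤ 0.05 and by magnitude-based inference on 90% limits, with no order of precedence, while a 5% level is claimed for everything. The 5% is therefore not guaranteed for every declared effect; that is different from saying it is exceeded in every case.

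The size depends on how *unclear* is read, and the results rest on 16 per arm, a between-arm contrast and assumed thresholds. The literal reading gives little or no inflation; its cost at about 0.2 SD or more is a significant finding labelled unclear. The permissive reading gives null declarations well above 5%.

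A reader might also infer that the rules can point in opposite directions. They cannot: the disagreement is between an effect and no effect, or between an effect and an unclear one.

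**What to change.** In the last paragraph of Incidence of response:

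1. State that the tests at p ≤ 0.05 are the only decision rule for VO2max and cardiometabolic effects.
2. Report 95% confidence intervals to match those tests.
3. Remove the clear/unclear magnitude-based verdict as a basis for conclusions. Keep any statement of magnitude as description only, showing the estimate and its 95% interval against one minimal important difference per outcome, stated in advance.

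This changes wording only; design, sample size and data collection stay as they are. Intervals become about 20% wider (2.042/1.697 = 1.20), and fewer effects will be described as clear. A single sentence making the tests decisive and the magnitude statements descriptive would resolve the hierarchy, but the 90% limits would still not match a 5% test, so the interval level should change with it.
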